## Safety reporting

### Reporting requirements

The collection and reporting of Adverse Events (AEs) will be in accordance with the Research Governance Framework for Health and Social Care and the requirements of the Health Research Authority. The chief investigators will assess the seriousness and causality (relatedness) of all AEs experienced by any study participant with reference to the protocol. Participants experiencing any AE will also be referred to their endocrinology consultant for further assessment and management if required.

### Adverse events

All medical occurrences, including symptoms of GHD and out of range laboratory and BMD values, which meet the definition of an AE will be reported. All AEs occurring during the study observed by the investigator or reported by the participant, whether attributed to study or not, will be recorded on the patient’s medical notes. The following information will be recorded: description, date of onset and end date, severity, assessment of relatedness to study, other suspect device and action taken. Follow-up information should be provided, as necessary.

AEs considered related to the study as judged by patient’s endocrinology consultant will be monitored until resolution, or until the event is considered stable. All related AEs that result in a participant’s withdrawal from the study or are present at the end of the study, will be followed up until a satisfactory resolution occurs. Any participant with a serious adverse event will undergo assessment by their endocrinology consultant and be given appropriate care under medical supervision until symptoms cease or the condition becomes stable. The severity of events will be assessed on the following scale: 1 = mild, 2 = moderate, 3 = severe. The relationship of AEs to the study will be assessed by participant’s endocrinology consultant.

Each severe (serious) AEs (SAEs) will be reviewed by the chief investigator and the participant’s endocrinology consultant who will classify the AEs into one of the following two categories:
**
*Suspected Unexpected Serious Adverse Reaction (SUSAR) (which may or may not be fatal or life threatening) and Suspected Serious Adverse Reaction (SSAR). Rare but recognised AEs will not be considered as ‘unexpected*
**’.

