#### Objectives

•To assess the rate of patient recruitment, retention and withdrawal.•To identify barriers for recruiting and retaining participants into the study.•To assess the suitability and acceptability for patients of the frequency of follow-up and assessment.•To assess the suitability and acceptability for patients of the QoL questionnaires.•To assess the study protocol including recruitment, biochemical monitoring, body composition monitoring, and QoL assessment.•To assess the safety of GH treatment discontinuation in adult patients with GHD.

**
*Study participants*
**

The study will recruit a total of three groups of adult patients with GHD (aged 25 years and over).
I.
**
*Group 1-
Discontinuation group*
**: 20–25 patients who have been on GH therapy for 5 years or longer and voluntarily agree to discontinue their GH treatment and be monitored for two years.II.
**
*Group 2-
Continuation group*
**: 20–25 patients who have been on GH therapy for 5 years or longer and voluntarily agree to take part in the study, where their GH treatment is continued and are monitored in the same way as the discontinuation group.III.
**
*Group 3-
Continuation group following initial discontinuation*
**: patients who were initially part of the discontinuation group (Group 1) and decided to withdraw from the study, due to adverse effects of GH discontinuation, and restart their treatment. Patients monitoring will continue in the same way as the continuation group for a total of two years from the time they initially enrolled in the study.

**
*Study Visits*
**

Visit 1

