### Reporting period

For each individual participant, details of all AEs will be documented and reported for the duration of participation in the study, i.e., from the point of consent up until the last follow-up visit. The investigator will report all SAEs to the sponsor immediately upon knowledge of the event. This will be done by informing the research and development office that a serious adverse event has occurred verbally or in writing which will be followed by a detailed written report on the event. This report will be kept in the Investigator Site File. The chief investigator and the participant’s endocrinology consultant will assess the seriousness and severity of AEs on behalf of the sponsor.

The sponsor will ensure that all relevant information about a SUSAR which occurs during the course of the clinical study and is fatal or life threatening is reported as soon as possible to the relevant Ethics Committee no more than seven calendar days after the sponsor was first made aware of the event. Any additional relevant information will be sent as soon as available.

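### The safety section treats severe as serious, gives an unrelated SAE no class and names two causality assessors, so counts of serious, related and SUSAR events will be unreliable until it is reconciled

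*Protocol article*

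**What the plan says.** One of the six Phase 2 objectives is "To assess the safety of GH treatment discontinuation in adult patients with GHD". The rules that feed it stand under Safety reporting in the protocol article.

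- **Reporting requirements:** "The chief investigators will assess the seriousness and causality (relatedness) of all AEs experienced by any study participant".
- **Adverse events, intensity:** "The severity of events will be assessed on the following scale: 1 = mild, 2 = moderate, 3 = severe".
- **Adverse events, causality:** "The relationship of AEs to the study will be assessed by" the participant's endocrinology consultant. The consultant's judgement also decides which AEs are followed as related.
- **Adverse events, SAEs:** "Each severe (serious) AEs (SAEs) will be reviewed by the chief investigator" and the consultant, "who will classify the AEs into one of the following two categories". The two categories are SUSAR and SSAR. Rare but recognised events are not to count as unexpected.
- **Reporting period:** the chief investigator and the consultant "will assess the seriousness and severity of AEs on behalf of the sponsor". All SAEs go to the sponsor.
- **Reporting procedure:** the annual report to the ethics committee covers all SAEs. A fatal or life-threatening SUSAR is reported within 7 days and other SUSARs within 15 days.

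**The concern.** Severity is how intense an event is. Seriousness is a separate attribute that decides whether the SAE pathway applies. If the two are merged, an intense but non-serious event can be counted as an SAE, and a serious event of moderate intensity can be left out.

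A classification with only suspected-reaction classes leaves no correct label for an event that both roles think has nothing to do with stopping or continuing GH. Such an event either goes unclassified, against the rule, or is filed as a reaction. If it is also treated as unexpected, it triggers an expedited report.

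Where two sections give the causality decision to different people, the related-event count depends on whose judgement was entered.

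The numbers at stake are the SAE count, the related-SAE count and the SUSAR count. With groups this small, they would be read closely when the future multi-centre study is planned.

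**Working it through.** The document states no event count, rate or power figure for safety, so there is nothing to reproduce. The check compares the sections with each other.

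**1. Severe and serious.** The intensity scale makes *severe* grade 3 of 3. Shortly afterwards the same section names SAEs as *severe (serious)* events. Reporting requirements, however, has seriousness assessed for all AEs, whatever their grade, and Reporting period lists seriousness and severity as two things to assess. Crossing the two attributes shows where the parenthesis does harm:

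| | Grade 3 | Grade 1 or 2 |
|---|---|---|
| Serious | SAE under either reading | SAE under the other sections; not an SAE under the parenthesis |
| Not serious | SAE under the parenthesis; not an SAE under the other sections | Not an SAE under either reading |

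Two of the four cells are classified differently according to which sentence is followed.

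**2. SAE classes.** An SAE can be unrelated, related and expected, or related and unexpected: three states. The rule offers two classes, SSAR and SUSAR, which fit the second and third. The first state is possible under the protocol's own terms, because AEs are recorded whether or not they are attributed to the study and relatedness is assessed for each. The annual report's mention of non-SUSAR events does not supply the missing class, because under the two-class rule the only non-SUSAR class is SSAR.

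The expectedness rule bears on where an unrelated SAE lands. Only recognised events are kept out of *unexpected*, and the risk section says that no serious and lasting effects are foreseen. An unrelated SAE of a kind not recognised for GH discontinuation is therefore more naturally pushed towards SUSAR than SSAR, which brings in the 7- or 15-day reports.

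**3. Who decides.**

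| Decision | Reporting requirements | Adverse events | Reporting period |
|---|---|---|---|
| Causality | Chief investigators | Consultant | Not addressed |
| Seriousness | Chief investigators | Not assigned separately | Both roles |
| SUSAR or SSAR | Not addressed | Both roles | Not addressed |

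No sentence says whose judgement prevails. This has practical effect: follow-up of related AEs depends on the consultant's view, while onward reporting belongs to the chief investigator.

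**4. Leverage of one misfiled participant.** Planned group size is 20 to 25. One participant is 1/25 = 4% to 1/20 = 5% of a group. This is the weight of a single error, not a forecast of how many will occur.

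**The case against.** The strongest reply is that the data survive the wording. Every AE is recorded regardless of attribution, with severity and relatedness as separate fields. Every SAE goes to the sponsor and into the annual ethics report. An unrelated SAE would still carry its own relatedness entry. The severe/serious merger is one parenthesis, and the text around it treats the attributes as distinct. Safety is one of six objectives in a study whose primary aim is feasibility, and categorical results are to be given as frequencies and percentages. Full AE and SAE definitions may stand in the complete protocol, and their absence from an article is no fault.

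Most of this stands, and it limits the consequence. It does not remove the contradictions. The two-class rule is a stated instruction that is wrong for unrelated events, and the two causality statements cannot both be followed when the roles differ.

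Three stronger readings are tempting, and the document does not support them:

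- **That the safety objective cannot be answered.** AEs by group, severity and relatedness can still be described.
- **That serious events of moderate intensity will be missed.** They could be if the parenthesis is followed, but seriousness is to be assessed for all AEs, so a miss is not built in.
- **That low IGF-1 will flood the discontinuation group with AEs.** The text does list reportable occurrences as "including symptoms of GHD and out of range laboratory and BMD values", and IGF-1 is measured at every visit. The sentence goes on, however, to limit reporting to occurrences that meet the AE definition. That definition is not in the article, and nothing there says that a low IGF-1 value alone would meet it.

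It is also true that a wrong expedited report arises only when an unrelated SAE is labelled unexpected, not for every unrelated SAE.

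**Conclusion.** The point holds as an internal contradiction with a limited consequence. Three defects are established from the text alone: severe is used as a synonym for serious against the neighbouring sections, an unrelated SAE has no valid class, and causality has two different owners with no rule for disagreement. Counts of serious events, related serious events and SUSARs will be unreliable until these are reconciled, and some unrelated SAEs may be reported as expedited SUSARs. The general AE description by group is not lost.

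The size in events cannot be derived, because the document gives no SAE or hospitalisation rate. The defects do not depend on such a rate. The exposure is bounded by the study size, at most 50 participants. The conclusion assumes that staff follow the article's wording as written. If the full protocol or the AE form already separates these attributes, the correction is confined to the article.

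**What to change.** Make four changes to Reporting requirements, Adverse events and Reporting period:

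1. Define seriousness by its own criteria, separately from the 1 to 3 intensity grade, and delete the *severe (serious)* wording.
2. Use three SAE classes: unrelated; related and expected (SSAR); related and unexpected (SUSAR). Only the third should lead to expedited reporting.
3. Name one role as responsible for causality throughout, and state how a disagreement between the chief investigator and the consultant is settled and recorded. Align the seriousness assessor in the same edit.
4. Before analysis, re-check the coding of all SAEs already recorded, by the same rule in every group. Because a serious event of lower intensity might not have been filed as an SAE, look through the remaining AEs for seriousness in the same pass.

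The cost is a protocol amendment through the sponsor's R&D department and the ethics committee, as the Amendments section requires, revised AE-form wording, and re-coding for at most 50 participants. Severity and relatedness are already recorded per event, so no new participant data are needed. Under Trial status, analysis starts four weeks after the last participant's final visit and the database is locked only after analysis, so the schedule leaves room for the correction.

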### Reporting period

For each individual participant, details of all AEs will be documented and reported for the duration of participation in the study, i.e., from the point of consent up until the last follow-up visit. The investigator will report all SAEs to the sponsor immediately upon knowledge of the event. This will be done by informing the research and development office that a serious adverse event has occurred verbally or in writing which will be followed by a detailed written report on the event. This report will be kept in the Investigator Site File. The chief investigator and the participant’s endocrinology consultant will assess the seriousness and severity of AEs on behalf of the sponsor.

The sponsor will ensure that all relevant information about a SUSAR which occurs during the course of the clinical study and is fatal or life threatening is reported as soon as possible to the relevant Ethics Committee no more than seven calendar days after the sponsor was first made aware of the event. Any additional relevant information will be sent as soon as available.

### Reporting procedure

The chief investigator is responsible for onward reporting of any AEs. A fully documented audit trail will be maintained at the study site. A report of all SAEs (including non-SUSAR events) will be submitted annually to the main Research Ethics Committee (REC).

AEs will be documented in the participant clinical notes. The chief investigator will evaluate any AEs reported and, if appropriate, will report further to the relevant authorities (Health Research Authority/Research Ethics Committee, UHB). The chief investigator will report a minimal dataset of all individual events categorised as a fatal or life threatening SUSAR to the Health Research Authority/Research Ethics Committee within 7 days. Detailed follow-up information will be provided within an additional 8 days.

For adverse events categorised as SUSARs, these will be reported within 15 days. A copy is also sent to the UHB Research Governance Team at the time of sending the SUSAR report. The Health Research Authority/Research Ethics Committee will be notified immediately if a significant safety issue is identified during the study, with the UHB Research Governance Team also notified at the same time.

Any study participants can contact the chief investigator by email (
[contact]) or by phone ([name]) at any point during the study (Monday to Friday, between 08.00H – 16.00H) to report any adverse events or concerns about taking part/continuing with the study.

## Amendments

Any amendments (substantial or non-substantial) will be approved by UHB R&D. The chief investigator will submit a notice of amendments to the REC for consideration and will report to the Health Research Authority/REC using the appropriate processes. Amendment history will be tracked at the end of the protocol (section 11.3), reporting the amendment number, protocol version number, date amended, and approval issued, author(s) of changes and details of changes made.

## Trial registration

The trial is registered (04.08.2023) with the National Library of Medicine
ClinicalTrials.gov, registration number
NCT05979480.

Protocol version: GAMBOL_STUDY_PROTOCOL-(Version1-2_20 March 2025).

## Trial status

Recruitment to this study started in July 20 2023 and completed in May 31 2024. Study participants are expected to complete the phase 2 of the study in May 31 2026. Phase 3 of the study is expected to be completed in June 30 2026. Analysis of the data from phase 2 of the study will commence 4 weeks after completion of the final study visit of the last study participant. Analysis of data from phase 3 of the study will commence 4 weeks after completion of the interview of the last study participant. Database will be cleaned and locked after the data analysis is completed. The current protocol version is Version1-2_20 March 2025.

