
**
*Data collection and analysis*
**

Data will be collected and stored in the study centre’s secured and password protected server. A GAMBOL study data sheet will be generated using REDCap® which is password protected. All data will be pseudo-anonymised. Data analysis will involve descriptive statistics and presented as means ± standard deviation (SD) for continuous variables that are normally distributed, and as medians with interquartile (25th and 75th percentile) range for continuous variables that are skewed. Between-group differences will be analysed using independent samples t test and analysis of covariance (ANCOVA) test. Categorical variables will be presented as frequencies and percentages. A statistician from UHB has agreed to provide support for this study.

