### Sampling

**
*Size of sample*
**

As this is a feasibility study, a formal power calculation is not required.
^20^ A maximum of 25 patients in each group (50 in total) will be recruited in the phase 2 which is at the upper end of the numbers recommended for pilot/feasibility studies.
^21^ 5–8 participants who completed the phase 2, and similar number of participants who withdrew from phase 2, will be invited to participate in the phase 3 of the study.

**
*Sampling technique and recruitment*
**

Phase 2 (Observational Feasibility Cohort Study): purposive case sampling will be used to recruit study participants. Eligible patients will be identified from endocrine outpatient clinic lists and from the endocrine database of patients on growth hormone treatment. Patients who are willing to take part in the study will be given the choice of taking part in either the discontinuation group or the continuation group. Patients withdrawing from the discontinuation group will be invited to continue on the study for on-going monitoring.

Phase 3 (Qualitative Study: Interview): purposive sampling will be used to recruit study participant. Participants will be recruited from those taking part in the phase 2 of the GAMBOL study. Participants will be approached at the point of completing the phase 2 (study visit 5), whereas those who are withdrawing from phase 2 of the study will be approached at the point of withdrawal.

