### Audit and inspection

The study will be monitored and/or audited by University Hospitals Birmingham NHS Foundation Trust under their remit as sponsor and other regulatory bodies to ensure adherence to Good Clinical Practice and the UK Health Policy Framework for Health and Social Care.

Monitoring of study data shall include confirmation of informed consent; source data verification; data storage and data transfer procedures; local quality control checks and procedures, back-up and disaster recovery of any local databases and validation of data manipulation. The study coordinator or where required, a nominated designee of the sponsor, shall carry out monitoring of study data as an on-going activity.

Once the first study participant is enrolled into the study and their first visit completed, the data and adherence to protocol will be monitored by the sponsor’s quality assurance (QA) team. Monitoring of study participants by the sponsor’s QA team will then occur at random intervals throughout the study which could be in the form of self-monitoring tools being supplied.

Study conduct will be subject to systems audit of the study record for: inclusion of essential documents; permissions to conduct the study; study delegation log; CVs of study members and training received; local document control procedures; consent procedures and recruitment logs; adherence to procedures defined in the protocol (e.g. inclusion/exclusion criteria, timeliness of visits), and accountability of study materials. This will be led by the chief investigator and reported back to the sponsor.

Entries on the data sheet will be verified by inspection against the source data. A sample of participants’ data (approximately 10%) will be checked on a regular basis for verification of all entries made. In addition, the subsequent capture of the data on the study database will be checked. Where corrections are required these will carry a full audit trail and justification.

Study data and evidence of monitoring and systems audits will be made available for inspection by the regulatory authority where applicable as required. The data and adherence to protocol will be monitored by the sponsor’s Q&A team at the earliest opportunity.

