Data provided by the participants for the study will be stored in paper and electronic forms in the study centre’s NHS computers and premises. The chief investigator and members of the GAMBOL study team will have access to medical records in order to document the patients’ participation in the study and any interventions carried out during the course of the research. A manual paper record of participant addresses, postcodes and telephone numbers will be maintained in the investigator site file (ISF) to enable correspondence or contact with participants during the course of the study. Contact will be related to the patient’s participation in the current research project only. The Trust’s laboratory and imaging department will store participants’ data on NHS servers. The ISF will be kept in a locked filing cabinet within a lockable office. Access to the ISF will be restricted to the GAMBOL study team only. No confidential information will be asked from the participants unless consent is given. Questionnaire data will be securely stored in the NHS server which is password-protected and encrypted in situ. No data will be transferred out of University Hospitals Birmingham NHS Foundation Trust. Data will be analysed by the GAMBOL study team and the UHB Trust statistician from the Trust password protected server.

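### The protocol cleans and locks the database after the analysis; the final clean and lock should come first

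*Protocol article*

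**What the plan says.** The sequence is set in the Trial status section of the protocol article. Phase 2 analysis "will commence 4 weeks after completion of the final study visit of the last study participant". The closing step follows in the same paragraph: "Database will be cleaned and locked after the data analysis is completed". This is current text for Version 1-2 of 20 March 2025, not an entry in an amendment log.

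Four other places bear on the point:

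- **Phase 2, Data collection and analysis:** descriptive summaries, and then "Between-group differences will be analysed using independent samples t test and analysis of covariance (ANCOVA) test".
- **Data protection and patient confidentiality:** "Data will be analysed by the GAMBOL study team and the UHB Trust statistician".
- **Sampling:** willing patients "will be given the choice of taking part in either the discontinuation group or the continuation group".
- **Audit and inspection:** data sheet entries are verified against source, capture in the study database is checked, and a sample of participants' data is checked regularly. On corrections it says: "Where corrections are required these will carry a full audit trail and justification".

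**The concern.** Final cleaning makes the data fit to analyse. Lock stops values from changing once results can be seen. If both come after the analysis, neither does its job for the results that are reported.

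One of two things then follows whenever the late clean changes a value. If the analysis is not rerun, the reported figures do not match the locked database. If it is rerun, the correction was made by people who already knew the group results, and it is hard to show that the results did not influence which queries were raised or how they were settled.

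The exposure covers the primary aim as well as the secondary one. Recruitment, retention and withdrawal counts depend on each participant's recorded status, including moves from Group 1 to Group 3, and a final clean would normally reconcile that status.

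**Working it through.** No sample size, power or alpha figure bears on this point, and the plan gives no figure to reproduce. The check is a reading of the order of events against every section on data checking and analysis.

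**Step 1. The order as written.** Last final visit, then 4 weeks, then analysis, then cleaning and lock. Phase 2 is expected to end on 31 May 2026, so on the stated schedule analysis begins about 28 June 2026 (31 May + 28 days). The article gives no purpose for the 4 weeks and does not make clean or locked data a condition for starting.

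**Step 2. Does another section put a clean or lock earlier?**

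| Section | Content | Final clean or lock before analysis? |
|---|---|---|
| Phase 2, Data collection and analysis | REDCap data sheet, descriptive statistics, t test, ANCOVA | No |
| Audit and inspection | Monitoring, source verification, capture checks, sample check, audit trail | No; these are ongoing checks |
| Data protection and patient confidentiality | Storage, access, who analyses | No |
| Trial status | Start of analysis; clean and lock | No; states the reverse |

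**Step 3. What the ongoing checks cover.** With 20–25 patients in each of two groups (40–50 in total), a 10% sample is 4–5 participants at a time. The check recurs, so coverage may build up if different participants are drawn. A separate, broader sentence says that data sheet entries will be verified against source, and the text leaves unclear whether the 10% sample limits it. On either reading these are running checks and not a closing clean with all queries resolved.

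**Step 4. What the audit trail does.** It makes a late change traceable and requires a reason for it. No rule bars a correction once analysis has begun.

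**Step 5. Leverage of one late correction.** This is arithmetic on the planned group sizes, not an estimate of error rates.

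- One participant whose status is reclassified moves a group's retention proportion by 1/25 = 4 percentage points, or 1/20 = 5 percentage points.
- One value corrected by an amount d moves a group mean by d/25, or by d/20.

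The documents give no error rate, so the number of such corrections is unknown and could be zero.

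**The case against.** The strongest reply is that the sentence is probably a drafting slip. The 4-week gap looks like time set aside for cleaning, and the data will have been monitored throughout. That may be so, but the article does not say it. This is also not a detail left to an unseen analysis plan: the article states a rule, and the rule is in the wrong order.

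A reader might infer more than the documents support:

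- **That the results will come from uncleaned data.** Audit and inspection describes source verification, checks on database capture and a recurring sample check. What is absent before analysis is a final clean and a lock, not all checking.
- **That the reported figures will certainly differ from the locked data.** This holds only if the late clean changes values and the analyses are not rerun. The article is silent on reruns.
- **That the study team can alter results unseen.** The Trust statistician shares the analysis, and corrections carry a justification and an audit trail. These controls do not prevent late edits, but they make them visible.
- **That the lack of blinding creates the problem.** Lock should precede analysis in a blinded study too. Self-chosen groups and the absence of any described blinding add exposure but are not the cause.
- **That Phase 3 has the same fault.** No transcript defect is shown. Interviews are transcribed verbatim, and each transcript is read against the recording before coding.

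The objection on severity stands. The primary aim is feasibility, metabolic, body composition and QoL effects are a secondary aim, and there is no formal power calculation.

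**Conclusion.** The point holds in a limited form. As written, the final clean and lock follow the analysis, and nothing elsewhere in the article corrects this. Phase 2 feasibility counts and group comparisons may therefore differ from the final locked data, or may be open to the charge that corrections were guided by the results.

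The importance is moderate: this should be fixed, but it does not threaten the study's main purpose. No numerical effect can be given, because it depends on how many values a late clean would change and whether the analyses would be rerun, and the documents state neither. The conclusion assumes that the sentence means what it says and that the full protocol, which is not shown, does not set a different order.

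**What to change.** Replace the sentence in Trial status with:

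*The Phase 2 database will be cleaned, all queries resolved and the database locked before any between-group analysis begins; any change after lock is documented and the affected analyses re-run.*

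Use the existing 4 weeks between the last final visit and the start of analysis for this work. The cost is one sentence of text. The downside is a possible short delay to the start of analysis if queries are still open when the 4 weeks end. If the full protocol carries the same sentence, it needs the same correction.
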